**Total score ≥ 4 predicts difficult intubation**			

### Outcomes

Outcome parameters will be measured before and after GA, and subsequently after 1 and 8 days. Possible differences can, thus, be assessed before and after GA, within each type of general anaesthesia, and between GA methods (sevoflurane vs. propofol).

#### Primary outcome

Volume and morphology of the brain’s anatomical structures as recorded by T1-weighted three-dimensional (T1w3D) anatomical MRI scans, and white-matter microstructure as measured using diffusion tensor imaging (DTI)

#### Secondary outcomes

Differences in resting-state functional MRI (rsfMRI)Severity and characteristics of fatigue, as measured by Multidimensional Fatigue Inventory (MFI-20) [42]Cognitive function including attention, speed, and executive functions as measured by computer-based neuropsychological tests (Paced Auditory Serial Addition Test (PASAT), Test of Attentional Performance (TAP) and Conners Continuous Performance Test, 3rd edition (CPT3))Quality of Recovery – 15-item questionnaire (QoR) [43]Correlations between MRI findings as well as clinical outcomes as described above

#### Exploratory outcomes

Global and regional cerebral perfusion and oxygen metabolism (CMRO_2_) as measured by Phase Contrast Mapping (PCM) and dual-echo arterial spin labelling (ASL)Cerebral metabolism as measured by MR spectroscopy (MRS) of metabolites such as lactateResponse to visual stimuli measured by Blood-Oxygen-Level-Dependent (BOLD) signal

### Setting

This study was scheduled to start on 1 September, 2019 and to be completed by 15 December 2020. It will take place at Rigshospitalet Glostrup, a part of Copenhagen University Hospital. Physical examinations, cognitive tests, questionnaires, GA and post-anaesthesia care will take place at the Department of Neuroanaesthesia. The MRI will take place at the Functional Imaging Unit, Department of Clinical Physiology, Nuclear Medicine and PET, Rigshospitalet Glostrup.

### Study setup

#### Inclusion and exclusion criteria (Table 1)

### General procedure

The study consists of an inclusion interview with a pre-study examination and two separate study sessions separated by 4 weeks. Each study session consists of one intervention day followed by two MRI days. See Fig. 1: Study flow chart for study sessions. Study session 2 mirrors session 1, the only difference being the type of GA on the intervention day (sevoflurane vs. propofol). Figure 2 is a populated Standard Protocol Items: Recommendations for Interventional Trials (SPIRIT) Figure, with a schematic presentation of the study elements.

**Fig. 1 Fig1:**
[figure not shown]
Flow chart for study sessions. Study session 2 mirrors session 1, the only difference being the type of GA on the intervention day (sevoflurane vs. propofol)

**Fig. 2 Fig2:**
[figure not shown]
Schematic presentation of the study elements

### Pre-study

#### Recruitment and inclusion

Participants will be recruited in Denmark by online advertisement and via magazines for medical students at the University of Copenhagen. Informed written consent from all volunteers will be obtained by a physician before inclusion in the study. The volunteer will be screened for eligibility according to the inclusion and exclusion criteria. Physical examination, airway assessment (pre-anaesthesia evaluation, including Mallampati- and Simplified Airway Risk Index (SARI)), electrocardiogram (ECG) and blood sampling (haemoglobin, sodium and potassium levels) are carried out. The volunteer will be informed that participation is voluntary and that they may withdraw from the study at any given time. Inclusion and physical examination are done by a physician. Informed consent for any ancillary studies will also be obtained by a physician. See Table 1 for inclusion and exclusion criteria.

#### Randomisation and blinding

This is a participant- and assessor-blinded study, whereas the personel involved in the maintenance of GA are unblinded regarding the anaesthetic agent. The order of sevoflurane or propofol is randomised by a random allocation sequence (simple randomisation), computer-generated by inhouse expertise and stored in sealed and opaque envelopes to secure adequate allocation concealment. Evaluation of data will be done separately, pseudonymised and without information regarding the GA. The questionnaires, MFI-20 and QoR, and the cognitive tests, are presented to the volunteers before randomisation and will be filled out by the volunteer without intervention from anyone having information regarding the GA.

### Study session 1

#### Intervention day (day 0): pre-intervention procedure

The volunteer will be re-screened according to all inclusion and exclusion criteria. It will be ensured that the volunteer is fasting according to the recommendations of The Danish Society for Anaesthesia and Intensive Care Medicine (DASAIM), which are aligned with the guidelines from the European Society of Anaesthesiologists [45]; thus, 2 h of fasting are required for clear liquids and 6 h for all other oral intake. After changing into hospital clothing, baseline MRI scans will be performed (MRI 1). Cognitive testing will be performed, and the questionnaires MFI-20 and QoR will be filled out by the volunteer.

#### General anaesthesia

The principal investigator and the specialist anaesthetic nurse will open the sealed envelope corresponding to the relevant session, and thereby assign the volunteer to GA with either sevoflurane or propofol, depending on randomisation. The volunteer remains blinded to GA type. The volunteer is placed on an operating table in the supine position, carefully adjusted to avoid localised pressure injuries during the GA. Monitoring equipment will be set up for continuous monitoring of heart rate (three-lead ECG) and peripheral oxygen saturation (pulse oximetry). Non-invasive blood pressure is monitored intermittently every 5 min. Body temperature is measured every 30 min with an ear probe. A heating blanket is used if the body temperature drops below 36.0 °C and turned off if the body temperature rises above 37.5 °C. Following intubation, end-tidal CO_2_ (ETCO_2_) is monitored by capnography. Two peripheral intravenous catheters will be inserted.

##### Induction

Regardless of the randomisation, GA is induced by an IV injection of propofol. To facilitate intubation, remifentanil will be infused simultaneously. Propofol and remifentanil will be infused by infusion pumps (B Braun Perfusor Space, B. Braun Melsungen AG, Hessen, Germany) set on target-controlled infusion modus (TCI). Both propofol and remifentanil dosage will be directed by the calculated effect-site concentration (i.e. the concentration of each type of medication in the brain). Propofol infusion rates will be calculated by Schnider’s pharmachokinetic model for propofol [46–48]. This will correspond to a propofol dose well within the routinely used range for induction of 1.5–2.5 mg/kg. Remifentanil infusion rates will be calculated by the Minto model [46]. This will correspond to a remifentanil dose within the routinely used range for intubation of 2.4–4 μg/kg body weight. The infusion rates will thus be based on age, gender, weight and height of each volunteer. TCI with effect-site concentration targets for both propofol and remifentanil ensures the correct infusion rates to obtain and maintain the intended concentrations of the medications at the effect-site (the brain) at any time during the GA. If necessary, additional boli of propofol 20 mg can be injected. Intubation will be performed by video laryngoscopy (McGrath™ MAC, Aircraft Medical Ltd., Edinburgh, UK). After intubation, remifentanil will be discontinued.

##### Maintenance

According to the randomisation, GA will be maintained either via continuous inhalation of sevoflurane or via infusion of propofol. Sevoflurane will be administered via the evaporator system on the ventilator (Dräger Primus®, Drägerwerk AG & Co, Lübeck, Germany). Sevoflurane dosage will be adjusted to 1. 5 mimimum alveolar concentration (MAC) or lower, which equals the routinely used dosage of sevoflurane for maintenance of GA. Infusion of propofol will be administered via the infusion pump (B Braun Perfusor Space, B. Braun Melsungen AG, Hessen, Germany). The infusion pump will continue the TCI directed by effect-site concentration using Schnider’s pharmacokinetic model for propofol, as described under ‘Induction’. This would correspond to a propofol dosage well within the recommended range for maintenance of anaesthesia with propofol (4–12 mg/kg body weight/h). However, higher infusion rates may occur, in particular during induction of GA. Both sevoflurane and propofol doses can be adjusted according to the clinical response of the volunteer. To ensure sufficient depth of GA, bispectral index (BIS) will be monitored and kept within the generally accepted values for GA (40–60) by adjusting the dosage of the anaesthetic agent. In addition, a brief test of response to benign pain will be carried out every 15 min: Pressure applied to the fingernail bed with an algometer (Somedic Algometer type II (Somedic SenseLab AB, Sösdala, Sweden)), and ulnar-nerve stimulation (post-tetanic count) with a standard neuromuscular monitor (Philips NMT on Intellivue, MP70 Anaesthesia). If the volunteer responds with any sign of pain perception (movement, lacrimation, or increase of heart rate or blood pressure), dosage of the anaesthetic agent will be increased, and the test repeated after 5 min. The volunteer will receive a background infusion of NaCl 0.9% during the induction and maintenance phases of GA. The dosage of NaCl will be well within the routinely administered range of 300–500 ml in total during the GA. Ventilation will be maintained via a ventilator (Dräger Primus®, Drägerwerk AG & Co, Lübeck, Germany), on ventilation modus volume autoflow. Inspiratory oxygen will be set between 30 and 45%, respiratory frequency (RF) 10–20/min and tidal volume of 6–10 ml/kg/min with a maximum peak pressure of 30 cmH_2_O. Optimal respiration will be ensured through continuous measurement of end-tidal CO_2_ (ETCO_2_ = 4.0–5.7 kPa), oxygen saturation (SpO_2_ = 94–100%) and airway pressures (PEEP 5–15 mmHg, peak pressure 30 mmHg). GA will be maintained for 2 h after intubation and terminated by stopping the administration of sevoflurane or propofol.

##### Extubation

The volunteer is expected to be ready for extubation at 10–30 min after discontinuing propofol or sevoflurane. They will then be transported to the post-operative care unit.

##### Post-intervention care

In the post-operative care unit, the volunteer will be continuously monitored with heart rate and SpO_2_, while blood pressure will be measured every 15 min. The volunteer will receive oxygen supplementation if needed. Monitoring, care, discharge and intake of food and drinks will adhere to DASAIM’s standard of post-operative care [49, 50]. The volunteers will be observed for at least 2 h. Then, cognitive testing and questionnaires will be repeated before MRI 2. After MRI 2 the volunteer will be allowed to leave the hospital, but will be instructed not to remain alone for the next 24 h as recommended by the American Society of Anaesthesiologists (ASA) [51].

##### Follow-up MRI scan day (+ 1 day)

One day after GA cognitive testing, questionnaires and MRI scans (MRI 3) will be repeated.

##### Follow-up MRI scan day (+ 8 days)

Eight days (7–10) after GA cognitive testing, questionnaires and MRI scans (MRI 4) will be repeated once more.

### Study session 2

Study session 2 will be initiated no earlier than 4 weeks after study session 1 (4 weeks after the intervention day), to ensure a sufficient wash-out period. Before the initiation of study session 2, the volunteer will be re-screened to ensure eligibility for continued participation. Session 2 will be identical to session 1, except that general anaesthetic will be changed from propofol to sevoflurane or vice versa.

#### Procedures for handling adverse effects during the clinical study

##### Monitoring of adverse effects

The volunteers will be monitored for possible adverse effects during GA and in the post-intervention care phase. Any adverse effects will be treated immediately, and the volunteer will be observed until the adverse effect is no longer present. If relevant, the volunteer will be referred to follow-up by a general practitioner. Thus, there will not be a follow-up for the known adverse effects listed below in the setting of this study. The volunteers will be advised to report any medical events during each of the study sessions (from the intervention day until completion of MRI 4 (7–10 days later). In the period between study sessions 1 and 2, the volunteers will not be monitored in any way. However, when registering for study session 2, the volunteers will be asked of any health or medically related events or changes since study session 1, cf. exclusion and withdrawal criteria.

##### Allergies and anaphylaxis

Any volunteer with known medical allergies will be excluded from the study. Should symptoms or suspicion of allergy including anaphylaxis arise, exposure will be stopped immediately, and the condition treated according to already implemented practice in the Department of Neuroanaesthaesiology, Neuroscience Centre, Rigshospitalet. The volunteer will be withdrawn from the study after relevant care, informed of the event and referred to the Danish Anaesthesia Allergy Centre for relevant follow-up. The suspected agent will be registered in the volunteer’s medical journal to avoid future exposure.

##### Hypotension

Hypotension will be defined as a mean arterial pressure (MAP) below 50 mmHg, or a 30% decrease from pre-induction blood pressure. In case of hypotension during GA, the blood pressure will be corrected by the following standard procedures in prioritised order: Trendelenburg position, IV fluid bolus of 300 ml NaCl, IV ephedrine 5–10 mg, IV phenylephrine 0.1 mg. Fluid, ephedrine and phenylephrine can be repeated as in standard procedures already implemented in Department of Neuroanaesthesiology, Neuroscience Centre, Rigshospitalet. In the case of persistent hypotension without effect of these means, anaesthesia will be terminated, and the volunteer withdrawn from the study after relevant care. The volunteer will be informed of the event and referred to a general practitioner for further assessment to ensure diagnosis and treatment of any underlying cause.

##### Pain

During the study mild pain may arise, which can be treated with paracetamol 1000 mg. Severe pain will be registered as an adverse event (AE) and the cause will be analysed to prevent recurrence. The participant will be treated according to established guidelines for managing severe pain in the Department of Neuroanaesthesiology.

##### Nausea and vomiting

Nausea and vomiting may occur as an adverse effect of the anaesthetic agents. In severe cases, this will be treated with ondansetron 1 mg which can be repeated if necessary, to a maximum of 8 mg. In the rare case of treatment failure by ondansetron, dehydrobenzperidol 0.625–1.25 mg can be administered.

### Adherence strategy and discontinuation of the study

The volunteers will be in close contact with the principal investigator throughout the study. Reminders of appointments and information will be sent by e-mail or SMS, and the volunteers will receive telephone calls for extra safety during the study sessions. The volunteers can reach the investigators by telephone and e-mail and are urged to call the investigators immediately at any time if questions, discomfort or any medical symptoms arise. In case of acute emergency, the volunteers should call the public emergency telephone number directly. If a volunteer does not complete the trial, an account should be given as to whether and how this participant is followed in the trial as well as what data has been collected from the participant. The volunteer may be excluded on their own request or as a result of violation of protocol, or if unforeseen circumstances mean that withdrawal from the study is in the participant’s best interest. Unblinding regarding anaesthesia type is permissible if necessary, for safety or medical reasons.

### MRI

All MRI scans will be performed with a 3-Tesla Philips Achieva d-stream with a 32-channel receive head coil. Each MRI scan consists of the following sequences: T1-weighted 3D anatomical MRI (T1w3D), diffusion tensor imaging (DTI), resting-state functional MRI (rsfMRI), BOLD functional MRI measurements after visual stimulation with checkerboard (block design), arterial spin labelling (ASL), Phase Contrast Mapping (PCM), MR susceptometry, MR spectroscopy, and technical scans (e.g. survey scan, B0 field map) needed to obtain sufficient data for performing analysis on the primary scans.

### Cognitive performance tests

The Test of Attentional Performance (TAP) in this study consists of Crossmodal Integration, Go/Nogo, Incompatibility and Flexibility. They measure cognitive integration, attention and flexibility in response to auditive and visual stimuli (TAP 2.3.1 12/2016 from Psytest, D-52134 Herzogenrath). The Paced Auditory Serial Addition Test (PASAT) measures auditive working memory [52]. Conners Continuous Performance Test, 3rd edition (CPT3) measures persistent attention (CPT3, MHS 2014).

### Quality of Recovery-15 Questionnaire and Multidimensional Fatigue Inventory

The volunteers fill in the validated Quality of Recovery Questionnaire (QoR-15) [43] and the Multidimensional Fatigue Inventory (MFI-20) [42]. The QoR-15 questionnaire results in a score of 0–150. The MFI-20 covers aspects of general fatigue, physical fatigue, mental fatigue, motivation and activity in 20 statements with five-scale ratings of agreement.

### Data collection and monitoring

MRI data will be kept on encrypted hard drives behind double-locked doors, as well as on a logged hard drive at the facilities of the Capital Region of Denmark. All other data will be registered in an encrypted, double-locked electronic case report form (eCRF) for each volunteer included in the study. Any AEs or effects will be registered in the eCRF and reported to the sponsor and relevant authorities. All data will be handled in compliance with General Data Protection Regulation (GDPR) and Danish law. The study will be monitored and audited by the Good Clinical Practice (GCP) units in Denmark [53]. Data will be destroyed after 10 years.

### Data processing – MRI

T1-weighted 3D anatomical images will be pre-processed using the FreeSurfer imaging analysis suite (http://surfer.nmr.mgh.harvard.edu/). Other software packages and approaches for data analysis may also be applied. Diffusion-weighted images will be pre-processed using the FSL software package (http://www.fmrib.ox.ac.uk and http://fsl.fmrib.ox.ac.uk/fsl/fsl4.0/tbss/index). This includes inspection of image quality. The resulting data will then be processed via dtifit and tract-based spatial statistic. The re-aligned images will then be fed into bedpostx for local modelling of diffusion parameters. Using bedpostx in conjunction with track-based statistics (TBSS) allows us to model for crossing fibres. The re-aligned images will be fed into probtrackx2 for tractography between the anatomical areas mentioned above. Other software packages and approaches for data analysis may also be applied. Resting-state fMRI (rsfMRI) scans will be analysed using FSL MELODIC (http://fsl.fmrib.ox.ac.uk/fsl/fslwiki/MELODIC). Pre-processing steps will include spatial smoothing, motion correction, slice time correction, high-pass filtering and brain extraction. Individual component analysis (ICA) using data-defined and no less than 60 ICAs will be applied. RsfMRI scans will be co-registered initially to the individual T1w3D anatomical scans (after neutral flipping and brain extraction) and subsequently to MNI 152 brain atlas. A full quality assurance (QA) will be performed consisting of inspection of head movement (< 3 mm and < 3°), acceptable co-registration and inspection of image quality. Resting-state networks (RSNs) will be identified using dual regression. Noise reduction will be performed manually. Randomise command will be performed with a design matrix consisting of the paired *t*-tests with and without co-variates, i.e. age and gender. Results will be displayed upon the MNI-152 normal brain atlas after dimension change as *p* < 0.05 after correction for multiple comparison. Activated areas will be identified semi-automatically. Additional software and methods for data analysis may be applied. In addition, age, gender, physiological variables, blood tests and cognitive test scores, etc. may be used as co-variates in the analysis.

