## Methods

### Study design

This study is a participant- and assessor-blinded, randomised, cross-over clinical trial. The study population is healthy volunteers with a male:female ratio 1:1. Inclusion will continue until 30 volunteers have completed the study (See Table 1 for inclusion and exclusion criteria). The intervention is 2 h of GA. On each of two intervention days, the volunteer will be exposed to GA by either TIVA (propofol) or by a volatile agent (sevoflurane). Each volunteer will receive both types of GA during the study, the order being determined according to randomisation. Participants will be blinded to the type of GA. The assessment of outcome will be blinded during analysis.

**Table 1 Tab1:** Inclusion and exclusion criteria

**Inclusion criteria**	**Exclusion criteria**

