### Statistical analysis

The distribution of continuous data is rated for normality using residual-plot or by the Shapiro-Wilk W test. Normality can be reached by simple transformation (log, logit). Statistical comparison of paired data is performed with parametric or non-parametric method or by analysis of variance (ANOVA). Depending on the distribution, testing is performed with Mann-Whitney or Wilcoxon tests, respectively. The risk for Type I errors is reduced by reducing the significance level to 0.05 (alpha). A general summation goal will be used to avoid mass-significance by repeated measurements. In statistical measurements where multiple comparisons cannot be avoided, Duncan’s corrections (i.e. secondary outcome parameters) are performed. For MRI data, correction for multiple comparisons is performed with Bonferroni’s correction or the false discovery rate (FDR). For statistical comparison between categorical variables (i.e. psychometric data) the *X*^2^ test with Yates’ correction is performed.

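### No period term is named for the sevoflurane–propofol contrast although the order is simply randomised; the paired test then loses power and, in an unbalanced split, carries part of any period effect

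*Protocol article*

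**What the plan says.** The design is a two-period cross-over. Protocol article, Study design: "Each volunteer will receive both types of GA during the study, the order being determined according to randomisation", and "Inclusion will continue until 30 volunteers have completed the study". Under Randomisation and blinding, "The order of sevoflurane or propofol is randomised by a random allocation sequence (simple randomisation"; no blocking or balancing of the two orders is described.

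The only group-level model set out in detail is in Data processing – MRI. It follows the sentence "Resting-state fMRI (rsfMRI) scans will be analysed using FSL MELODIC" and reads "Randomise command will be performed with a design matrix consisting of the paired" t-"tests with and without co-variates, i.e. age and gender". The same section adds that "physiological variables, blood tests and cognitive test scores, etc. may be used as co-variates in the analysis". For everything else, the Statistical analysis section says "Statistical comparison of paired data is performed with parametric or non-parametric method or by analysis of variance (ANOVA", and lists no model terms. No section names period, sequence or carry-over.

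Two features already protect the comparison. Session 2 starts no sooner than four weeks after the first anaesthetic. MRI, cognitive tests and questionnaires are also taken before anaesthesia in each session, so every session supplies its own baseline.

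**The concern.** A paired test of sevoflurane against propofol treats the order of the sessions as irrelevant. If volunteers change differently in session 2 than in session 1 whatever the agent, each paired difference carries that period effect, with a plus sign in one order and a minus sign in the other. With equal orders the effect cancels from the mean but inflates the variance. With unequal orders part of it stays in the estimated agent effect, and simple randomisation does not prevent unequal orders.

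The likeliest source is practice. The cognitive battery is taken four times per session, eight times in all. If gains flatten with repetition, the gain from the first test to tests 2–4 will exceed the gain from the fifth test to tests 6–8. Subtracting the session baseline does not remove that. The covariates named for the paired matrix, age and gender, are the same for a volunteer in both sessions (age to within weeks), so they cannot remove it either.

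**Working it through.** **The plan's own figure.** Detection of differences between general anaesthesia methods gives a 10% difference, SD 10%, alpha 0.025 and power 80%, hence n = 20. The formula n = 2(z₀.₉₈₇₅ + z₀.₈₀)² × (10/10)² = 2 × (2.241 + 0.842)² = 19.01, rounded up to 20, reproduces it. This is an independent-groups, per-group formula. That is a separate matter and does not affect what follows. The SD of the within-volunteer difference is not stated. I take two readings: 10% (agent effect 10/10 = 1.0 SD), or 10 × √2 = 14.14% for two uncorrelated changes (agent effect 10/14.14 = 0.71 SD).

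**Model.** Let d be a volunteer's change under sevoflurane minus the change under propofol, each from its own session baseline. Then d = τ + πs + e, where τ is the agent effect, π is the session 2 minus session 1 difference in change, and s is +1 if sevoflurane came second and −1 if it came first. A constant shift between sessions has already cancelled. The size of π is not in the documents; 0.5 and 1.0 SD of d are assumptions.

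**Bias given the split.** The mean of d estimates τ + π(n₁ − n₂)/30. From Binomial(30, 0.5):

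- exactly 15:15 has probability 0.144, and the bias is 0;
- 19:11 or worse has probability 0.200, and at least 8/30 = 27% of π enters;
- 20:10 or worse has probability 0.099, and at least 10/30 = 33% of π enters.

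**Type I error at nominal 0.025** (simulation, unadjusted paired t-test):

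| Period effect | All allocations | 19:11 or worse | Remaining splits |
|---|---|---|---|
| 0.5 SD | 0.025–0.026 | about 0.06 | 0.017 |
| 1.0 SD | 0.025–0.026 | about 0.10 | 0.007 |

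The columns agree: 0.2 × 0.06 + 0.8 × 0.017 = 0.026, and 0.2 × 0.10 + 0.8 × 0.007 = 0.026. With a period term the rate stays at about 0.025 in every split.

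**Power, averaged over simple randomisation, N = 30, alpha 0.025:**

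| Agent effect | Period effect | Paired t-test | With period term |
|---|---|---|---|
| 0.71 SD | 0 | 0.93 | 0.92 |
| 0.71 SD | 0.5 SD | 0.86 | 0.92 |
| 0.71 SD | 1.0 SD | 0.65 | 0.92 |
| 1.0 SD | 0 | 0.998 | 0.998 |
| 1.0 SD | 0.5 SD | 0.993 | 0.998 |

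A hand check gives the same picture. Left unmodelled, π raises the SD of d by √(1 + π²), so 0.71 becomes 0.707/1.118 = 0.63 or 0.707/1.414 = 0.50. Multiplying by √30 and subtracting the critical t of about 2.36 leaves 1.10 or 0.38, that is, power of about 0.86 or 0.65.

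In percentage points, with an SD of 14.14%, these period effects are 7.1 and 14.1 points. The second exceeds the planned 10-point agent difference. At 2 and 5 points the unadjusted power is 0.92 and 0.90.

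**Age and gender.** If the matrix has a column per volunteer, a covariate constant within volunteer adds no rank. On difference scores, a mean-centred age or gender column leaves the estimated mean difference unchanged and can only explain variation between volunteers. Neither form removes π.

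**The case against.** The strongest reply is about scope. The quoted matrix belongs to resting-state fMRI, a secondary outcome. A reader might infer that the whole cross-over, including the primary T1-weighted and DTI outcomes, is fixed to a paired test without period. The article does not say that. For those outcomes the Statistical analysis section allows an ANOVA without listing its terms, so period is unstated rather than excluded, and a fuller plan may include it. This stands.

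A reader might also infer that session differences in general bias the agent comparison or inflate its error rate. They do not. The session-specific baseline removes any constant shift. Over repeated randomisation the paired contrast is unbiased and holds its level. The inflated rates apply only to the unbalanced fifth of allocations, and the other splits run below nominal. A between-session difference in change is also much less plausible for brain volume or DTI than for cognition.

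Two further readings go too far. Age and gender are offered with and without, are legitimate on difference scores, and are nowhere presented as a period adjustment. Rank deficiency would arise only if volunteer columns were also fitted, which the article does not say. Cognitive scores are optional covariates, and correlating them with MRI findings is a declared secondary outcome. Nothing states that post-anaesthesia scores will adjust the agent effect, though the wording does not rule it out.

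What remains is that the one matrix actually specified has no period column, the order is not balanced by design, and no section supplies the term.

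**Conclusion.** The point holds as a recommended change of moderate weight. The general cost is power. It is small at the planned effect unless the period effect is large: from 0.92 to 0.86 at 0.5 SD, and to about 0.65 in the extreme 1.0 SD case, if the agent effect is 0.71 SD. It is negligible at 0.5 SD if the agent effect is 1.0 SD. The second cost depends on the realised split. With a one-in-five chance, 27% or more of the period effect enters the contrast, and type I error is about 6% or 10% instead of 2.5%.

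These sizes rest on assumed period effects, on the SD of differences being 10% or 14.14%, on normal errors and on 30 completers. The documents give no basis for choosing among the period effects. The concern is greatest for the cognitive tests.

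**What to change.** State that sevoflurane and propofol are compared on change from each session's own baseline, with period in the model.

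- **Resting-state fMRI (randomise):** analyse the within-volunteer differences with an intercept and one order column coded +1/−1. Do not mean-centre that column; otherwise the intercept reverts to the raw mean difference and keeps the bias. Age and gender may stay as optional mean-centred covariates but do not replace it.
- **Other outcomes:** name period as a term in the ANOVA, or use a mixed model with agent and period fixed and volunteer random. The mixed model also keeps volunteers with only one session, whom the Missing data section says are to be included.
- **Covariates:** in models of the agent effect, use pre-anaesthesia values only, and keep post-anaesthesia cognitive scores for the correlation aim.

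No new data are needed. The cost is one degree of freedom and a variance factor of 1/(1 − ((n₁ − n₂)/30)²), which is 1.125 at 20:10. If there is no period effect, that is about 1–2 points of power on average (0.93 to 0.92 at 0.71 SD). Power with 30 volunteers stays above 80% at the planned effect: about 0.89 at 20:10 with the larger SD.
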